#### Relevant Concomitant Care Permitted or Prohibited During the Trial

There is no relevant concomitant care, permitted or prohibited during this trial.

#### Criteria for Discontinuing or Modifying Allocated Interventions

Participants can withdraw their consent to participate at any time, before or during the study. Incomplete survey data will not be used in the primary analysis, except at a meta-level to report the aggregate number of incomplete surveys.

#### Provisions for Posttrial Care

This trial involves the viewing of a short, animated storytelling video featuring fish, after which a collection of validated surveys will be completed by participants in both groups. The trial will be conducted purely online.

There are no foreseeable risks associated with participating in this study. Participants volunteer and consent to participate in the study and are aware that they can withdraw at any time. The study investigators can be contacted at any time after the study, should the participants wish to follow up.

#### Plans for Assessment and Collection of Outcomes

The Qualtrics platform will collect data submitted by individual participants as they select their responses to the surveys used in this trial. We anticipate completing all data collection within a 6-week period.

#### Data Management

Qualtrics uses Transport Layer Security encryption for transmitted data. Qualtrics’ services are hosted by trusted data centers that are independently audited using the industry-standard Statement on Standards for Attestation Engagements 18 (SSAE-18) method. The research team conducting this study can access only anonymized data and, for statistical analysis purposes, we will download and safely store this data on secure computers maintained by our coinvestigators.

#### Statistical Methods for Analyzing Primary and Secondary Outcomes

##### Descriptive Statistics

We will use descriptive statistics to summarize the distribution of our outcomes by demographic factors, including age, gender, race/ethnicity, political affiliation, socioeconomic status, and previous experience with both addiction and childhood trauma, since these factors could affect scores.

##### Primary Outcomes

For each participant, stigma scores will be calculated individually. The mean score for each study arm at T1 and T2 will be calculated and compared between the intervention arms and the control arm at T1, and between the intervention arms and the control arm at T2, using repeated measure ANOVAs. This will be done at the study level and the country level to identify differential effectiveness across geographic conditions. We will also use multilevel regression analyses to control for demographic factors and other potential variables as needed. All analyses will be conducted in R (R Core Team, 2021).

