### Randomization, Consent, and Study Design

After reviewing the Institutional Review Board-approved information sheet, delivered to prospective participants online via ProA, those who indicate their consent to take part in the study will then be randomly assigned to one of three groups:

Intervention A: receiving the SAS video full intervention group.Intervention B: receiving the SAS video partial intervention (without sound) group.Control Group: receiving written information about addiction prevalence.

A baseline survey will be used to collect demographic information as well as baseline data on our primary and secondary outcomes. Thereafter, the Intervention A group will watch the 2.5-minute video, the Intervention B group will watch the 2.5-minute video without sound, and the control group will read a fact sheet about the global burden of addiction. Following this, all groups will complete a series of validated questionnaires to assess our primary outcome: addiction stigma, and secondary outcomes: optimism, warmth toward the subject, and hopefulness.

We will conduct the first round of surveys immediately post exposure of the intervention groups to the SAS video interventions and the control group to their written fact sheet. Follow-up assessments, using the same surveys, will be conducted 2 weeks later. To ensure the accuracy and validity of the results, we will include attention checks and exclude participants who fail these checks. Each participant will spend approximately 8 minutes watching the intervention and completing the surveys and will receive US $4.80 for completing the study. Figure 1 represents the trial design and flow.

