#### Sample Size

We calculated the sample size needed for comparing mean scores between the 3 arms, as detailed in the trial design. This was performed independently for the primary and secondary outcomes based on the score of each survey, upon which we selected the most conservative sample size for our study.

We assume that a significant, sustainable change in addiction stigma from watching the SAS video could be achieved by multiple exposures to the video or similar SAS interventions in a series of “micro-doses.” As our study measures the effect of a single exposure to a single SAS video, we aim to measure a small change in our mean outcome scores, presuming that these small changes could yield larger ones following repeated exposures (microdoses). Thus, we have powered this trial to detect a small effect size for comparing the mean scores between trial arms, that is, *d*=0.1, smaller than the generally recommended threshold for detecting a small effect size [31].

We used the sample size formula for a 1-tailed comparison of the mean scores with equal variance, a Type I error of 0.01 to account for multiple comparisons, and a power of 80% to detect changes in the mean scores. This resulted in a sample size of 1128 individuals per arm. Accounting for a potential attrition rate of 20% (personal communication with ProA), this yields 1410 individuals per arm. For this study, we will recruit 1500 participants per arm in each of the 3 countries. This gives us a total sample size of 13,500 participants, which allows us to detect the potential effects of the intervention with a power higher than 80%.

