### Secondary Outcomes

For the evaluation of secondary outcomes, we will use the statistical methods described above to evaluate both the immediate and medium-term effects of the SAS video intervention. The methods include, but are not limited to, *t* tests for independent groups, matched *t* tests for dependent groups, repeated measure ANOVAs, and multilevel regression models. For that, we will analyze the mean scores of the stigma surveys at T1 and T2, with a focus on the impact of the SAS video intervention on the score outcomes. All analyses will be conducted in R.

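### Own-baseline stigma is measured in everyone, but the primary analysis is described through T1 and T2 means and does not commit to adjusting for it, so precision is given up

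*Protocol article*

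**What the plan says.** Under Randomization, Consent, and Study Design: "A baseline survey will be used to collect demographic information as well as baseline data on our primary and secondary outcomes". Participant Timeline places baseline, viewing and the T1 surveys together in Step 1, so the baseline score comes shortly before T1.

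Under Primary Outcomes in the statistical methods: "The mean score for each study arm at T1 and T2 will be calculated and compared between the intervention arms and the control arm". The tool is repeated measures ANOVA, applied both to the whole study and by country. The same section adds "multilevel regression analyses to control for demographic factors and other potential variables as needed". The Analysis section likewise describes between-arm comparisons at T1 and at T2. For the secondary outcomes the article says "we will analyze the mean scores of the stigma surveys at T1 and T2", and lists independent and matched t tests, repeated measures ANOVA and multilevel models.

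The Sample Size section has no baseline term: "We used the sample size formula for a 1-tailed comparison of the mean scores with equal variance", with "a Type I error of 0.01 to account for multiple comparisons, and a power of 80% to detect changes in the mean scores". The target is d = 0.1, with 1500 recruited per arm in each country.

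**The concern.** A participant's own baseline score on the same questionnaire is usually a far better predictor of the post-exposure score than demographics are. Using it as a covariate removes the part of the outcome variance that it explains, and with it the effect of chance baseline differences between arms.

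That matters for a target as small as 0.1 SD. With 1500 per arm, the standard error of a chance baseline difference between two arms is sqrt(2/1500) = 0.037 SD, so differences of up to about ±0.07 SD (1.96 × 0.037) are unremarkable. A comparison of post-exposure means carries the correlated part of that difference into the result. This is the same loss of precision seen from another side, not an additional one.

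What is at stake is efficiency, mainly in the by-country comparisons, together with a covariate choice that is left open in the primary analysis.

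**Working it through.** **Inputs from the protocol article.** d = 0.1 (SD = 1), one-tailed alpha 0.01, power 80%, stated n 1128 per arm, attrition 20%, and 1500 recruited per arm per country (all from Sample Size). After attrition: 1500 × 0.8 = 1200 per arm per country at T2. Pooled over three countries: 4500 per arm, or 3600 after attrition.

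**Assumption.** r, the correlation of the baseline score with the later score, is not in the article. It is shown as a range.

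**1. The plan's own figure.** The article says "This resulted in a sample size of 1128 individuals per arm". From its stated inputs:

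n = 2 × (2.326 + 0.842)² / 0.1² = 2007.2, so 2008 per arm.

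The 1128 does not reproduce. The attrition step does: 1128 / 0.8 = 1410.

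**2. Power without baseline.** Power = Φ(d × sqrt(n/2) − 2.326).

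- 1200 per arm: Φ(2.449 − 2.326) = 54.9%
- 1500 per arm: Φ(2.739 − 2.326) = 66.0%
- Pooled, 3600 per arm: Φ(4.243 − 2.326) = 97.2%
- Pooled, 4500 per arm: Φ(4.743 − 2.326) = 99.2%

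**3. Power with baseline as a covariate.** The residual SD becomes sqrt(1 − r²), so power = Φ(d × sqrt(n/2) / sqrt(1 − r²) − 2.326) and the required n = 2007.2 × (1 − r²). For a change score the SD is sqrt(2(1 − r)).

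| r | n per arm for 80% (ANCOVA) | T2, 1200 per arm, ANCOVA | T1, 1500 per arm, ANCOVA | T2, 1200 per arm, change score |
|---|---|---|---|---|
| no adjustment | 2008 | 54.9% | 66.0% | – |
| 0.3 | 1827 | 59.5% | 70.7% | 39.9% |
| 0.5 | 1506 | 69.2% | 79.8% | 54.9% |
| 0.6 | 1285 | 76.9% | 86.4% | 66.0% |
| 0.7 | 1024 | 86.5% | 93.4% | 79.8% |
| 0.8 | 723 | 96.0% | 98.7% | 93.9% |

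**4. Correlation needed for 80% in a country.** r = sqrt(1 − n/2007.2).

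- T2, n = 1200: sqrt(1 − 0.598) = 0.63
- T1, n = 1500: sqrt(1 − 0.747) = 0.50

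The T1 column takes all 1500 as analysed. Exclusions for failed attention checks or incomplete surveys would lower it.

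**The case against.** The strongest reply is that the article never says baseline will be left out. The additional regression is open to other variables, so it is not limited to demographics, and the baseline score could be one of them. A repeated measures ANOVA could also take baseline as a level. The article keeps people without T2 data in the immediate-effect analysis, and for them baseline is the only other measurement. It also lists matched t tests for the secondary outcomes. Exact model terms may sit in an analysis plan that is not shown. An unadjusted randomised comparison is unbiased in any case.

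Much of this stands. A reader might infer that baseline data are discarded; the text does not establish that. What remains is that every analysis section names T1 and T2, none names the baseline score, and a covariate admitted only where needed is a choice left open. Reading baseline in as a level of the ANOVA would not settle the matter either, if it amounts to a change-score comparison: at r = 0.5 that gains nothing over ignoring baseline (54.9% at T2, against 69.2% with ANCOVA), and at r = 0.7 it gives 79.8% against 86.5%.

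A reader might also infer that adjustment restores the planned power or decides whether it is reached. The documents do not support that. The article gives no r. The shortfall exists only at country level, and it comes from the 1128 figure, which adjustment does not correct.

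**Conclusion.** The point holds as one of efficiency and prespecification. Baseline scores are planned for everyone, and the primary analysis as described does not commit to using them as a covariate. The comparison stays valid, but by-country precision is given up: the outcome variance would fall by r², that is by 25, 36, 49 and 64% at r = 0.5, 0.6, 0.7 and 0.8.

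Whether adjustment lifts a country-level comparison to 80% depends on r being at least about 0.63 at T2 or about 0.50 at T1. At r = 0.5 or 0.6 the T2 comparison improves but stays below 80%. These results assume d = 0.1, one-tailed alpha 0.01, equal variances, 20% loss at T2 and no loss at T1.

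**What to change.** State as the primary model either an ANCOVA at each time point or one longitudinal mixed model, with own-baseline score as a covariate (its effect allowed to differ by time), country as a fixed factor, arm, and arm-by-time. Take A versus control, B versus control and A versus B at T1 and at T2 from that model. For the by-country analyses, fit the same model without the country term. If the mixed model is chosen, reconcile it with the rule that people without T2 data enter only the immediate-effect analysis; separate ANCOVAs fit that rule as written.

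Use the same approach for secondary outcomes that have a usable baseline. Settle the hope item first: its prompt asks how hopeful the person feels after the video (or the fact sheet, for controls), so it cannot be asked unchanged before exposure.

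Correct the 1128 calculation separately. If baseline adjustment is credited in a revised calculation, state the assumed r and its source.

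The cost is protocol wording only, because the baseline survey is already planned. The article reports that no data had been collected as of March 2025. The change should be fixed before outcome data are analysed.

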#### Analysis

At the first time point (T1), we will compare addiction stigma, optimism, hope, and warmth toward subject scores between the 2 intervention groups and the control group. This comparison is intended to establish the immediate effect of watching the intervention videos on addiction stigma, optimism, hope, and warmth toward people with addiction. At the second time point (T2), we will once again compare our primary and secondary outcomes between the intervention and control groups. This will allow us to detect potential short-term effects of watching the intervention video on addiction stigma, optimism, hope, and warmth toward people with addiction. By comparing the outcomes of the 2 intervention arms at the 2 time points, we will be able to measure the contribution of sound design to the effect of the SAS video intervention.

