#### Methods for Additional Analyses (eg, Subgroup Analyses)

Exploratory subgroup analyses will be conducted to understand the extent to which demographic characteristics and country location moderate the effects of the intervention on stigmatization and secondary outcomes.

We will also use regression models to describe the potential effects of demographic factors on participant engagement. To quantify this engagement, we will use Qualtrics to offer participants voluntary posttrial access to the SAS video intervention. We will record a timestamp when the participant reaches the end of the second time point, the moment when a participant chooses to play the video and the moment when they end the study. Participants who skip the video or watch it for less than 3 seconds will be considered as not having engaged with the video. For the participants who watch the video, we will record the length of time spent watching it.

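### Repeating the arm-versus-control tests in each country does not test whether effects differ between countries, and a per-test 0.01 does not hold an assumed 5% family-wise level over the 16 primary-outcome tests this creates

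*Protocol article*

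**What the plan says.** Under Statistical Methods, Primary Outcomes, the protocol article compares mean stigma scores of the intervention arms with control at T1, and again "between the intervention arms and the control arm at T2, using repeated measure ANOVAs". It then adds: "This will be done at the study level and the country level to identify differential effectiveness across geographic conditions". The multilevel regressions named next are there to control for demographic factors and other variables. No arm-by-country term is mentioned.

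Under Methods for Additional Analyses, country appears again with a different status: "Exploratory subgroup analyses will be conducted to understand the extent to which demographic characteristics and country location moderate the effects of the intervention".

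The Analysis section adds the contrast between the two video arms: "By comparing the outcomes of the 2 intervention arms at the 2 time points, we will be able to measure the contribution of sound design". It does not say whether this is repeated by country.

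The only statement on error rate is in Sample Size, as a design input: "a Type I error of 0.01 to account for multiple comparisons". The calculation there is one-tailed. No family of tests, family-wise level or decision rule is given.

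**The concern.** There are two linked problems.

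First, the method does not fit the stated purpose. Three within-country tests give three answers on whether an effect was detected. A difference in effectiveness is a contrast between country-specific effects, and none of those three tests estimates it. When power in each country is moderate, one country can reach significance and another miss it although the effect is the same in both. Cross-country performance is central to the trial's hypotheses, so a reader could take such a split as a geographic finding.

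Second, the country repetition multiplies the primary-outcome tests by four, while one level of 0.01 is described as accounting for multiple comparisons. The text does not say which comparisons it is meant to cover.

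**Working it through.** **Inputs from Sample Size:** d = 0.1, one-tailed 0.01, 80% power, 1128 per arm before attrition, 20% attrition, 1500 recruited per arm per country. Evaluable n per arm per country therefore runs from 1500 × 0.8 = 1200 to 1500.

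**The plan's own figure.** 1128/0.8 = 1410 reproduces. The 1128 does not: 2 × (2.326 + 0.842)²/0.1² gives about 2008 per arm. That is a separate matter. It is noted here only because it explains why per-country power below falls short of 80%.

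**Split verdicts under an identical effect.** Power in one country is p = Φ(0.1 × √(n/2) − 2.326). The probability that one or two of three countries are significant is 1 − p³ − (1 − p)³.

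- n = 1200: p = Φ(2.449 − 2.326) = 0.549; split probability 1 − 0.165 − 0.092 = 0.743.
- n = 1320 (1500 at the pilot's 88% retention): p = 0.596; split probability 0.722.
- n = 1500 (T1, before exclusions): p = 0.660; split probability 0.673.
- At the nominal 80% power: 1 − 0.512 − 0.008 = 0.48.

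If the analysis adjusts for baseline with an assumed baseline–outcome correlation r, the effect is divided by √(1 − r²). For r = 0.5 to 0.7 the split probability becomes 64% to 35% at 1200 per arm and 48% to 18% at 1500 per arm.

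**A direct test of the difference.** For a 0.1 SD difference in effect between two countries, the standard error is √(4/n). Power at two-sided 0.05 and n = 1200 is Φ(0.1/0.0577 − 1.960) = 0.41.

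**Number of primary-outcome tests**, counting each arm contrast at each time point as one:

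- Primary Outcomes as written: 2 arms versus control × 2 time points × 4 analysis sets (pooled plus 3 countries) = 16.
- Adding the contrast of the two video arms, pooled only: 16 + 2 = 18.
- Adding that contrast in every country as well: 3 × 2 × 4 = 24. This is an inference.

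**Family-wise error at 0.01 per test.** With a 5% target (assumed), 0.05/0.01 = 5 tests. The simulations are under the null. They allow for the shared control arm, the overlap of pooled and country data, and a T1–T2 correlation assumed between 0 and 0.9. Ranges span one- and two-sided testing.

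| Tests | Bonferroni bound | Simulated |
|---|---|---|
| 4 pooled | 0.04 | 0.03–0.04 |
| 6 pooled | 0.06 | 0.04–0.05 |
| 16 | 0.16 | 0.09–0.13 |
| 18 | 0.18 | 0.10–0.14 |
| 24 | 0.24 | 0.13–0.18 |

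The country repetition accounts for most of the excess over 5%.

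**The case against.** Country moderation is planned, and moderation is ordinarily tested as an interaction. The model can be left to an analysis plan, as can the definition of the test family. That is fair as far as missing detail goes. It does not remove the mismatch in what is stated: Primary Outcomes assigns the question of country differences to the repeated country-level comparisons, while the other section calls that question exploratory.

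No sentence says that discordant p-values will be read as geographic differences. A reader might infer that the plan will report noise as differential effectiveness. The text sets no such rule, so this is a risk that the wording leaves open, not a stated procedure.

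A reader might also take 24 as the number of tests. The primary-outcome text gives 16, and 24 requires the sound contrast to be repeated by country, which is not stated. Nor does the protocol state a 5% family-wise target, so 0.01 cannot be called a failed 5% procedure without that assumption.

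The 74% is the top of a range, close to the formula's maximum of 75% at p = 0.5. It falls with full T1 numbers and further with baseline adjustment.

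Finally, the trial hypothesises effects in three countries and recruits its per-arm target in each. A ban on country-level significance claims does not follow from the point above; a structured scheme could keep them.

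**Conclusion.** The point holds in this form. The repeated country-level comparisons cannot do what Primary Outcomes says they are for, and that text conflicts with the exploratory status given to country moderation elsewhere. With the protocol's d = 0.1 in every country and one-sided 0.01, without baseline adjustment, split verdicts on one contrast would occur in about 67% to 74% of trials with no true difference. Baseline adjustment could lower this substantially, depending on the correlation.

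On multiplicity, the conclusion is conditional. If 5% family-wise is intended and country-level tests carry confirmatory claims, 0.01 per test gives about 9–13% over the 16 explicit tests, and 13–18% over 24 if the sound contrast is repeated by country. If only the four to six pooled contrasts are confirmatory, 0.01 is roughly adequate at about 3–5%. The protocol does not say which applies. The first part of the point stands whatever view is taken of multiplicity.

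**What to change.** In Primary Outcomes, replace the purpose clause: test differential effectiveness with the arm-by-country interaction in the pooled, country-adjusted model. Report country-specific effects with confidence intervals, and state that differences will not be inferred from one country being significant and another not. Bring the additional-analyses section into line on whether country moderation is exploratory.

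Name the pooled contrasts as the confirmatory family, either with Holm at 5% or at 0.01 each with the 4–6% bound stated (four or six contrasts). Then either label country-level tests descriptive or place them in a stated gatekeeping or Holm scheme. The choice is the sponsor's, given the per-country hypotheses.

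The cost is analysis wording, with no new data and no change in recruitment. Stand-alone country significance claims become weaker or are dropped. The interaction test has limited power, about 41% for a 0.1 SD difference between two countries at two-sided 0.05 and 1200 per arm, so a non-significant interaction should not be read as equal effects. That is a further reason to rely on estimates with intervals.
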